Additional calculations for Aim 2 are based on comparing observed changes in self-reported behaviors between arms using a t-test with adjustment for within-group correlations as described above. For these calculations, we assume changes will be computed as binary indicators of decrease in risk-taking behavior between the initial and final visits (e.g., a decrease in self-reported unprotected sex, or in the annual number of sexual partners). We also assume that the background prevalence of individuals reporting a decrease in risk-taking behavior ranges between 10% and 50%, and that the between-cluster coefficient of variation in prevalence within arms is 0.2. With these assumptions, our planned sample size should provide 80% power to detect prevalence ratios comparing prevalence of behavior change in the combined intervention group to that in the control group in the range .55-.7 at the 5% significance level. This corresponds to absolute differences in prevalence between arms of .07 – x.15, indicating that we should have sufficient power to detect relatively small differences between groups for a range of observed changes in high-risk behaviors.

Formal sample size calculations are not presented for Aims 3 or 4 because detailed preliminary information on the joint distribution of behavioral (including characteristics of participation) and our primary and secondary outcomes do not exist, and because the analyses proposed for these aims (described in section D.11.) are exploratory in nature. Since these analyses may involve estimation of interactions, we will clearly have reduced power compared to the analyses for Aims 1 and 2. However, we anticipate that power will be adequate to detect important associations.

1.b. Sample Size – Qualitative Component

Adolescent Girl Participants: Forty main study participants (20 from the intervention arm and 20 from the control arm) will be selected for participation in the qualitative interviews. As participants are enrolled into either study arm, every 5th girl in both arms will be selected for participation. The 40 participants will be interviewed 3 times for the duration of the study for a total of 120 interviews.

Interviews from an additional 10 participants enrolled in the Prevention for Positives component (5 from each arm, randomly chosen from the new cohort of 50) will be added to explore the feasibility of the study to include and support HIV and HSV-2 positive participants.

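### The Aim 2 power statement points in the harm direction, its ratio and difference disagree at the 10% end, and its 80% power is not reproduced over the stated 10–50% range

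*Protocol*

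**What the plan says.** All of the statement is in the Aim 2 paragraph of Protocol section 1.a. Sample Size – Quantitative.

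- Endpoint: "we assume changes will be computed as binary indicators of decrease in risk-taking behavior between the initial and final visits".
- Control rate: "background prevalence of individuals reporting a decrease in risk-taking behavior ranges between 10% and 50" per cent.
- Clustering: "the between-cluster coefficient of variation in prevalence within arms is 0.2", with the within-group adjustment already described for Aim 1.
- Claim: "our planned sample size should provide 80% power to detect prevalence ratios". The effect is given as "prevalence ratios comparing prevalence of behavior change in the combined intervention group to that in the control group in the range .55-.7", at the 5% level.
- Translation to the absolute scale: "This corresponds to absolute differences in prevalence between arms of .07 – x.15". The stray letter may come from text extraction, and nothing here rests on it.

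The paragraph concludes that power suffices for relatively small differences across a range of behaviours. Study Aims gives Aim 2 the same hypothesis as Aim 1, which is benefit from the combined intervention. The Data Analysis section analyses the same indicator of decrease as a between-arm difference in proportions.

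**The concern.** The endpoint, the ratio and the difference have to describe one effect, and here they do not. If an event is an improvement, the hypothesis predicts more events in the intervention arm and a ratio above 1. This is more than labelling, because power for two proportions depends on the rates themselves: 10% vs 5.5% is a different problem from 10% vs 18.2%.

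The risk behaviours are the declared secondary outcomes, and the section also uses Aims 1 and 2 as the benchmark when it describes power for Aims 3 and 4. A reader who accepts 80% power for differences of 7 to 15 points could give a null behavioural result more weight than it can bear.

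**Working it through.** **Inputs.** 150 per arm (Subject Selection, Numbers). Groups averaging 25 girls (1.a, Aim 1), so 150/25 = 6 per arm. Coefficient of variation k = 0.2 and control rates of 10–50% (1.a, Aim 2). Loss of 20% is stated for Aim 1 only, so results are shown with it (m = 20 evaluable per group) and without it (m = 25). The 5% level is stated without sidedness; two-sided is assumed. The Protocol does not say which ratio goes with which control rate. I pair .55 with 10% and .70 with 50%, because a lower base rate needs a more extreme ratio and .50 × .30 gives the stated .15.

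**Direction.** A ratio of .55–.7 for the prevalence of improvement means 30–45% fewer intervention girls improve.

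**Ratio against difference.**
- 50% end: .50 × (1 − .70) = .15. Agrees.
- 10% end: .10 × (1 − .55) = .045. The Protocol gives .07.
- Inverted to benefit: .10/.55 − .10 = .082 and .50/.70 − .50 = .214, against .07 and .15.

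**Attempt to reproduce 80%.** The Hayes–Bennett formula for proportions, solved for power with c = 6:

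V = [p0(1−p0) + p1(1−p1)]/m + k²(p0² + p1²); power = Φ(|p0 − p1| × √((c−1)/V) − 1.96)

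The c−1 reflects the formula's extra cluster. The favourable variant uses c in its place.

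10% vs 5.5%:
- m = 20: V = .141975/20 + .04 × .013025 = .00762. Then .045 × √(5/.00762) − 1.96 = −0.81, power 21%.
- m = 25, no extra cluster: V = .00620. Then .045 × √(6/.00620) − 1.96 = −0.56, power 29%.

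50% vs 35%:
- m = 20: V = .4775/20 + .04 × .3725 = .03878. Then .15 × √(5/.03878) − 1.96 = −0.26, power 40%.
- m = 25, no extra cluster: V = .0340. Then .15 × √(6/.0340) − 1.96 = 0.03, power 51%.

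The same formula for each reading, stricter to favourable case:

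| Reading | 10% control | 50% control |
|---|---|---|
| Literal ratios | vs 5.5%: 21–29% | vs 35%: 40–51% |
| Inverted ratios (benefit) | vs 18.2%: 35–47% | vs 71.4%: 55–66% |
| Stated differences as benefit | vs 17%: 28–38% | vs 65%: 32–40% |

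**Without clustering**, two-sided, the literal ratios give about 26% and 65% at 120 per arm, and about 31% and 75% at 150 per arm.

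**Detectable benefit at 80% power with clustering.** From 10%: to 23.2–26.6%, i.e. +13 to +17 points, ratio about 2.3–2.7. From 50%: to 75.6–79.6%, i.e. +26 to +30 points, ratio about 1.5–1.6.

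**The case against.** Several points on the other side stand.

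- **Part of the statement is consistent.** The upper difference of .15 agrees exactly with .70 at 50%. The lower can be matched in the benefit direction too: 10% to 17% is .07, with an inverse ratio of .10/.17 = .59, inside .55–.7. But then the upper end fails, since .50/.65 = .77. No single orientation fits both ends.
- **The pairing is mine.** Ratio .55 at a 50% control rate gives 76–88% power with clustering, so some effects in the ratio range do come near 80%. That effect is a difference of .50 × .45 = .225, however, outside the stated .07–.15.
- **Other assumptions help in places.** Ignoring clustering, the inverse of .70 at 50% has about 93–97% power. Literal .70 at 50% reaches 84% one-sided with no loss. Dropping clustering contradicts the paragraph's own method. At the 10% end the nearest approach is 10% vs 3%, about 79.5%. That needs one-sided testing, no loss and no clustering, and its ratio of .30 is outside the stated range.
- **The direction may be a slip of wording.** Data Analysis also compares the prevalence of the risk behaviours themselves at follow-up visits, where a ratio below 1 is benefit. A reader might infer that an analysis would run the wrong way. It would not, because the planned comparison is a difference in proportions.
- **Aim 2 is secondary.** The total of 300 is justified on HSV-2, and General Study Design reports main-study enrolment complete at 315.

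**Conclusion.** The paragraph is wrong as written in three limited respects: the ratio points to harm for an event that is an improvement; ratio and difference disagree at the 10% end; and 80% power is not reproduced over the stated range. Under the plan's clustering, power for the literal paired ratios is about 21–51%, and for the inverted ratios about 35–66%. This rests on the pairing, two-sided 5%, 6 groups of 25 per arm, and loss of either 0 or 20%.

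A reader might go further and say that true power is one figure of roughly 20–65%, that none of the ratios and differences agree, or that 300 participants are too few for every stated effect even without clustering. The documents do not support these. The first mixes different readings and models, the second overlooks the match at .15, and the third fails for several effects at a 50% control rate. Nor does the Protocol plan to read null results as proof of no effect; that risk lies in later interpretation. The statement should be corrected, but it does not undermine the primary analysis.

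**What to change.** 1. Restate the Aim 2 effect in the benefit direction with ratios above 1, or base the calculation on the prevalence of the risk behaviour itself, where a ratio below 1 is benefit.
2. Replace both ranges with detectable values that match each other under the plan's clustering: about +13 to +17 points (ratio about 2.3–2.7) at a 10% control rate and about +26 to +30 points (ratio about 1.5–1.6) at 50%. Say which value belongs to which control rate.
3. State the loss to follow-up and the sidedness assumed for Aim 2.
4. Delete the closing claim that relatively small differences can be detected.

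The cost is a recalculation and a rewritten paragraph. Sample size, endpoints, tests and conduct are unchanged. The drawback is that the stated detectable effects become less favourable.

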**4. Methods**

**A. General Study Design**

We propose a randomized controlled trial of an intervention combining a vocational training package -- including a conditional stipend and completion bonus -- with life-skills education and social support, compared to life-skills education alone. The study will begin with six months of start-up activities, and enrollment will take place within a six-month period at the beginning of the study. The economic livelihood intervention and life-skills programs will be administered for one year and participants will be followed for one year post-intervention. Data collection and service provision to participants will be provided through a health clinic and occasional visits using a mobile clinic. The frequency of intervention visits (i.e. visits related to the intervention program such as life-skills training, SHAZ reunions, and vocational training) is described below. Visits for data collection, including biological and behavioral outcome data, will be collected at baseline, and every six months thereafter for a total of five visits over the three year period. We will follow participants for one year after the intervention to ensure sufficient power to examine our primary outcome (Aim 1) as well as to establish the temporal association between the intermediary effects of increased economic opportunity and improved sexual negotiation skills in enhancing participants’ control over sexual interactions (Aim 3). Finally one year of follow-up will allow us to assess the intervention’s sustained effects on high-risk behavior (Aim 2). (Please see appendices: Intervention Design and Study Design Flow Chart)

**Prevention for Positives component:** The SHAZ main study has completed its enrollment for the ongoing intervention study, with a total of n=315. In order to assess the feasibility of implementing this intervention with HIV and HSV-2 positive clients, we will enroll an additional cohort of n=50 according to the same criteria as was used in the main study, except that those who are HIV and/or HSV-2 positive also will be eligible to enroll.

In order to meet this objective, we will contact and invite all participants who screened out of the study because of positive results (n=40) and invite these to re-screen for the study. We will then continue to recruit additional participants until we meet the desired sample size n=50.

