#### Methods of Data Analysis

**1.a. Sample Size – Quantitative**

Sample size calculations for Aim 1 assume that the background annual incidence rate for HSV-2 is 16% (corresponding to a prevalence rate following two years of follow-up of approximately 22%), and that participants will be followed for three years. Further, we conservatively assume that 20% of participants will be lost to follow-up (our average loss to follow-up over all completed studies is 12% [C.1]). Although individuals will form the unit of randomization, the fact that they will be associated via membership in life skills cohorts may induce correlation between individual outcomes within groups (assumed to include an average number of 25 girls) –We account for this using methods described in Hayes and Bennett [77], which take into account both the number of individuals randomized into each arm and the between-group variation in incidence rates induced by within-group correlation in infection outcomes. Incidence rates will be compared between arms using a two-sample t statistic adjusted to account for this source of variation. The corresponding coefficient of variation is assumed to be 0.2, a conservative estimate similar to values used in other studies [77, 78]. With these assumptions, our proposed sample size **of 300 (150** individuals randomized to each arm) will provide 80% power to detect a relative reduction in HSV-2 incidence as small as .53 at the 5% significance level. This corresponds to a 47% reduction in HSV-2 incidence (from 12% to 6.3%). Because unintended pregnancy is expected to have similar, if not higher incidence rates, the above calculations apply to this outcome as well.

Similar calculations for the HIV infection outcome (at 8% prevalence) indicate that we should have 80% power to detect a relative risk comparing incidence in the intervention group to the control group as small as .29 at the 5% significance level. This corresponds to a 70% absolute reduction in HIV incidence, assuming a background annual HIV incidence rate in the target communities of approximately 4%. This is an effect we do not expect to be able to detect given our sample size. We will, however, be able to report trends. The high prevalence rates cited in section B.1. were among young females in an antenatal clinic who were obviously sexually active and practicing unprotected sex. Among adolescents in Zimbabwe, HSV-2 rates tend to be three to five time higher than HIV rates [10].

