Household Heads: For each participant invited to undergo an in-depth interview, researchers will also interview their household head if the household head agrees to an interview. The 40 household heads will be interviewed one time only during the study for a total of 40 interviews.

Community and Youth Forum Members and Community Leaders: Four Community Advisory Board members (CAB) and two Youth Forum (YF) members will be interviewed every eight months for duration of the study; 3 interviews/participant providing a total of 24 interviews. One-time interviews will carried with identified community leaders (including religious leaders) or other key adult residents of Chitungwiza; the total number is not yet determined. Two key persons or trainers from each of the training institutions (3 identified institutions) working in partnership with the SHAZ! Study will be interviewed at three different times for the duration of the study providing a total of 18 interviews.

Adult Men: 30 adult men will be randomly selected for in-depth interviews. Men will be recruited from three identified locations where Zimbabwean men socialize and relax: beerhalls, sports clubs and at local “braais” or barbeques where informal sports games are often also played. Counting every fifth person who arrives ten men/location will be recruited. Interviewers will then secure a private time and place where in-depth interviews can be held.

2. Data Analysis

The primary analysis for Aim 1 will be based on an intent-to-treat comparison of HSV-2 incidence across treatment arms using Poisson regression methods to account for duration of follow-up. Individuals (the primary unit of randomization) will be the basic unit of analysis in these comparisons. However, we will control for correlation in incidence between peer support groups using generalized estimating equation (GEE) regression methods [85] appropriate for clustered outcomes. A similar approach will be taken to compare rates of unintended pregnancy and HIV infection across arms.

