**C. Subject Selection**

i. Main Study

**1. Who and Why**: The target population for the study is out-of-school adolescent female orphans living in urban -Zimbabwe. Females aged 16 to 19 years will be recruited. We restricted the intervention to females because prevalence data clearly show that girls are at higher risk for HIV infection. We hypothesize that an economic livelihood intervention will have greater effect on our biological and behavioral outcomes in females, as it will create alternatives to transactional sex, which is overwhelmingly practiced by females for accessing resources and gaining status. Sixteen is the legal age of consent in Zimbabwe, thus, we are able to collect and test biological specimens and provide results without obtaining parental or /guardian consent. We have chosen our upper age range as 19 because this is consistent with literature on the definition of adolescents [69]. We have restricted our sample to those girls not currently in school, and who have not already graduated from secondary school. The vulnerability of out of school girls (reflected through current HIV trends) also indicates a lack of access to: knowledge of health risks, skills in communication and negotiation, and to condoms and youth friendly services, which provide needed services at a convenient time and place, in a manner that satisfies adolescents’ concern over confidentiality [70, 71].

**2. Numbers**: One hundred fifty individuals will be randomly assigned to the treatment arm and 150 to the control arm, for a total of 300 participants.

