- Utilize UZ-UCSF Programme referral protocols for positive study participants to facilitate access to national treatment services.
- Modify data collection tools to assess additional clinicial, behavioral, social and biological outcomes as appropriate.
- Incorporate ‘living positively’ tenants to all participants at Shaz reunions. Examples might include urban gardens and nutrition tips, etc.
- Adding qualitative interviews (and observations of Lifeskills sessions) among both control and interview participants (5 interviews each group, randomly selected, repeated over time) within the new cohort to assess issues such as group dynamics during, especially disclosure, stigma/discrimination and confidentiality.

Outcome measures to be added include:

- Clinical assessment of HIV related opportunistic infections including weight gain/loss
- CD4 counts to assess disease progression and need for referrals for treatment (CDV<250)
- Measures of disclosure, social support, experience of stigma or marginalization at home and in the community through supplemental questionnaires administrated during counseling sessions, qualitative interviews and observations of life skills sessions.

As the intervention and control trainings are designed for an initial group of 25 participants, a training session will begin each time that number of participants is achieved in a given arm. The intervention, which will be delivered in the first year of the study, will consist of five main components: 1) Life Skills education (UZ-UCSF) and basic home-based health care training (Red Cross) (intervention and control arm) 2) Guardian support 3) Choice of vocational training options as determined appropriate and available by SHAZ! guidance counselors (plus stipend/bonus, intervention only); 4) Guidance counseling for social support (intervention arm only) 5) Ongoing SHAZ reunions. There will be one year of follow-up during which time the reunions and study visits will be on-going every six months. (See intervention overview for details).

B. Overview of Intervention

i. Intervention Group

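### The primary Poisson GEE rests on about 12 peer-group clusters with no small-sample correction stated; in its standard form it rejects a true null about 10% of the time, not 5%

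*Protocol*

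**What the plan says.** Under 2. Data Analysis, the primary Aim 1 analysis is an "intent-to-treat comparison of HSV-2 incidence across treatment arms using Poisson regression methods to account for duration of follow-up". Individuals are the unit of analysis, and "we will control for correlation in incidence between peer support groups using generalized estimating equation (GEE) regression methods". Unintended pregnancy and HIV are to be handled similarly, and GEE is used again for the Aim 2 behaviour outcomes. No variance estimator, small-sample correction, working correlation or reference distribution is given.

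The number of clusters follows from three other places:

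- Section 1.a, Sample Size – Quantitative: life-skills groups are "assumed to include an average number of 25 girls".
- Section F.1, Study Procedures: "a training session will begin each time that number of participants is achieved in a given arm". Groups are therefore nested within arm.
- Section C, Subject Selection: "One hundred fifty individuals will be randomly assigned to the treatment arm and 150 to the control arm, for a total of 300 participants".

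Section A, General Study Design, reports the enrolment reached: "The SHAZ main study has completed its enrollment for the ongoing intervention study, with a total of n=315".

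Section 1.a states detectability "as small as .53 at the 5% significance level" and describes the comparison differently from the analysis section: "Incidence rates will be compared between arms using a two-sample t statistic adjusted to account for this source of variation".

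**The concern.** The GEE sandwich variance is justified when the number of clusters is large. With about 6 clusters per arm it has two faults. It is biased low, because the residuals are taken around rates estimated from the same few clusters. It is also noisy, so comparing the Wald ratio with a normal quantile ignores the uncertainty in the standard error. Both faults make p-values too small and intervals too narrow.

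What is at stake is the false-positive rate of the HSV-2 test and of the pregnancy test, which is also a primary outcome under Aim 1. The same approach carries over to HIV and Aim 2.

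**Working it through.** **Cluster count.** 150 / 25 = 6 groups per arm, 12 in total. With the 315 enrolled, 315 / 25 = 12.6. This treats the peer support groups of the analysis section as the 25-girl life-skills classes.

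**The plan's own figure.** Section 1.a gives 80% power at a rate ratio of 0.53 and a 5% level (taken here as two-sided). The Hayes-Bennett formula for rates, solved for power with c groups per arm, is

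z_power = √{ (c − 1)(λ0 − λ1)² / [ (λ0 + λ1)/y + k²(λ0² + λ1²) ] } − 1.96

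The stated inputs are λ0 = 0.16, λ1 = 0.53 × 0.16 = 0.0848, k = 0.2, 3 years and 20% loss, so y = 25 × 0.8 × 3 = 60 person-years per group. Then √{5 × 0.005655 / (0.00408 + 0.00131)} − 1.96 = 0.33, or 63% power (71% with c in place of c − 1). A value near 80% (79.7%) appears with 12% a year, 3 years, no loss, k = 0 and c in place of c − 1. That mismatch is a separate matter. The figure at issue here is the 5% level.

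**Why 12 clusters matter, in closed form.** Take the two-arm Poisson model with a person-time offset and independence working correlation. Let arm a have D_a events over T_a person-years, with rate r_a = D_a/T_a. Group j has residual e_aj = d_aj − r_a·T_aj. The sandwich variance of the log rate ratio is Σ_a Σ_j e_aj² / D_a². The leverage of each group is h = T_aj/T_a, about 1/6.

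- Uncorrected: uses e². On average this is too small by a factor of about 1 − 1/6 = 5/6.
- Kauermann-Carroll: uses e²/(1 − h), a factor of 6/5, which removes that bias.
- Mancl-DeRouen: uses e²/(1 − h)², a factor of 36/25 = 1.44.

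With equal groups the Kauermann-Carroll ratio behaves approximately as t on 10 df. The size of each test then follows from the t(10) tail. The simulated column is a null simulation with 12% a year, 2 years, 20% loss, CV 0.2 and 6 groups of 25 per arm.

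| Test at nominal 5% | Cut-off on the t(10) scale | t(10) approximation | Simulated |
|---|---|---|---|
| Uncorrected sandwich, z | 1.96 × √(5/6) = 1.789 | 10.4% | 10.0% |
| Uncorrected sandwich, t(10) | 2.228 × √(5/6) = 2.034 | 6.9% | 6.5% |
| Kauermann-Carroll, z | 1.96 | 7.8% | 7.4% |
| Kauermann-Carroll, t(10) | 2.228 | 5.0% | 4.7% |
| Mancl-DeRouen, z | 1.96 × √(1.44 × 5/6) = 2.147 | 5.7% | 5.4% |
| Group-level t test, 10 df | 2.228 | 5.0% | 4.8% |
| Poisson ignoring clustering, z | – | – | 6.7% |

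**Sensitivity of the uncorrected z test.**

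- True correlation: 9.6-10.1% at CV 0 under independence. The excess comes from the number of clusters, not from the size of the correlation.
- Incidence of 16% a year at CV 0.2: 9.8-10.4% under independence, with equal or unequal groups.
- Exchangeable working correlation with unequal groups: 10.7-11.5%.
- Groups per arm: 5 gives 11.3%, 7 gives 8.8%, 8 gives 8.6% and 20 gives 6.2%.

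**Power.** At a rate ratio of 0.53, 12% a year and 2 years, nominal power is about 56% for the uncorrected z test and about 40-43% for the corrected tests. Part of the 56% is bought by running the test at about 10%.

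**The case against.** The strongest reply is that the protocol does not choose the uncorrected sandwich with a normal reference. It says GEE and stops, and the estimator and reference distribution are commonly left to the SAP, which is not shown. Implementations equally consistent with the text hold the level: Mancl-DeRouen with z, or Kauermann-Carroll with t(10). This stands. A reader might infer that the protocol has fixed a true type I error of 10-11%; it has not. What remains is that the method it names, in its standard form, is anti-conservative at the cluster count its own design implies.

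A reader might also see the t statistic in Section 1.a and the GEE in the analysis section as a flat contradiction. That is too strong. The t statistic sits in the sample-size section, only the analysis section names a primary analysis, and sizing on a simpler approximation is ordinary practice. Still, Section 1.a says how rates will be compared, so the two statements need reconciling.

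Nor does Section 1.a already prescribe a test on group-level rates with (groups − 2) degrees of freedom. It mentions neither, and the analysis section makes individuals the unit of analysis.

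Lastly, it is tempting to say that the result decides what controls are told. No section says so. The eligibility and consent sections tie the deferred economic component to a successful result, while the Control Group section offers vocational training to every control who completes a final visit, without that condition.

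The cluster count is an inference, since no section states it. Smaller peer support groups would mean more clusters and less inflation.

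**Conclusion.** The concern holds as a risk of the named method. With about 12 clusters, a standard Poisson GEE (uncorrected sandwich, normal reference) rejects a true null about 10% of the time at the plan's inputs, roughly twice the stated 5%. At the assumed CV of 0.2 that is worse than ignoring the clustering (6.7%). Changing only the reference to t(10) leaves about 6.5%.

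This rests on peer support groups being the 25-girl classes, on a two-sided 5% test, and on no correction being specified elsewhere. It does not depend materially on the assumed correlation or on the choice between 12% and 16% incidence. The simulated rates given here are for incidence outcomes at HSV-2-like rates. The Aim 2 comparison of proportions was not simulated, so for Aim 2 the same direction is expected but its size is not established.

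**What to change.** In 2. Data Analysis, keep the Poisson GEE and state the small-sample correction together with its reference distribution. Either of these holds the level:

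- Mancl-DeRouen variance with a normal reference (about 5.4%).
- Kauermann-Carroll variance with t on (groups − 2) degrees of freedom (about 4.7%). The t reference is essential, because with a normal quantile this variance still rejects about 7.4%.

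Alternatively, name as primary a two-sample t test on peer-group incidence rates with (groups − 2) degrees of freedom (about 4.8%). This changes the unit of analysis from individuals to groups, and the text should say so.

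Reword the t-statistic sentence in Section 1.a so that it either describes the sizing method only or matches the chosen primary test. Apply the same rule to pregnancy, HIV and Aim 2.

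The change is a sentence or two and a software option, to be settled before analysis. The real cost is wider intervals and the fall in nominal power shown above, part of which was an artefact of the inflated test.
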